## Abstract

**Background**: Vascular access in emergency departments (ED) is challenging for patients with difficult venous access (DIVA), causing delays and discomfort. Ultrasound-guided techniques may offer improved outcomes, making it crucial to assess their benefits, risks, and the effectiveness of validated identification systems. **Objectives**: To contribute new evidence regarding the effectiveness of validated tools for identifying DIVA and to assess the clinical benefits of ultrasound-guided vascular access in emergency care, and to assess their utility in arterial puncture for arterial blood gas sampling, from now on ABG, within the ED. **Methods**: This study follows the Standard Protocol Items: Recommendations for Interventional Trials (SPIRIT) guidelines for protocol development and the Consolidated Standards of Reporting Trials (CONSORT) guidelines for the conduct and reporting of the randomized clinical trial (RCT). The trial will be conducted in Spain throughout 2025. The study population will consist of 114 subjects with difficult intravenous access (DIVA), identified using the DIVA scale for individuals under 14 years of age and the A-DICAVE scale for adults, along with 80 subjects from the general surgical area (GSA). Participants will be randomly assigned, in a 1:1 ratio, to either the Control Group (CG) (traditional technique) or the Experimental Group (EG) (ultrasound-guided technique). Data collected will include sociodemographic characteristics, procedure-related variables (e.g., time required, human resources, and materials used), as well as pain levels, assessed using validated scales (EVA, FLACC, PAINAD), and overall satisfaction from both patients and healthcare professionals. Ethical approval has been obtained, and the trial will be registered as an RCT through an official clinical trial registry before recruitment begins. **Results**: Expected results suggest ultrasound guidance will significantly improve first-attempt success rates, reduce procedural time, enhance patient comfort, and optimize resource utilization compared to traditional techniques. **Conclusions**: The integration of ultrasound-guided vascular access into routine emergency protocols could enhance patient safety, satisfaction, and procedural efficiency in emergency care settings.

## 1. Introduction

Approximately 90% of patients who attend emergency departments (EDs) require venipuncture, with short peripheral intravenous catheters (PIVCs) being the most commonly used invasive devices in these settings [1]. Despite its routine nature, vascular access can be particularly challenging in a subset of patients, even for experienced healthcare professionals. When two or more attempts are required to achieve successful cannulation, patients are typically classified as having difficult intravenous access (DIVA) [2]. Repeated failed attempts are associated with damage to venous and arterial structures, increased pain and distress for the patient, delays in diagnosis and treatment, and greater consumption of healthcare resources [3,4]. Several studies have examined the clinical and demographic factors associated with DIVA. Conditions such as obesity, hypotension, generalized edema, advanced age, and the presence of multiple hematomas have been frequently cited as risk factors for cannulation failure [5,6]. Among adult populations, the prevalence of DIVA has been estimated to range between 10% and 24% [1]. In pediatric settings, the prevalence is even higher, with reports indicating that approximately 37% of children may fall into this category [7].

To address the challenges of early identification, a number of clinical tools and scoring systems have been developed. The first of these, the DIVA scale, was validated by Yen et al. for use in pediatric populations and aimed to guide clinical decision making from the point of triage [8]. This approach was later expanded by Kuensting et al., who incorporated additional variables such as the patient’s clinical history, the anticipated treatment plan, and the skill level of the staff performing the procedure [9].

In adult populations, the A-DIVA scale, introduced by van Loon et al. in 2016, provided a framework for identifying patients at risk of difficult venous access in surgical settings [10]. More recently, Salleras et al. developed the A-DICAVE scale, a simplified and ED-appropriate tool designed to support early recognition of DIVA and promote the use of ultrasound-guided techniques in these cases [11,12].

Despite increased attention to peripheral venous cannulation, few studies have investigated the early identification of patients with anticipated difficulties in arterial puncture, such as those requiring arterial blood gas (ABG) sampling. In these cases, ultrasound-guided techniques offer an opportunity to improve procedural success, enabling better visualization of target vessels and real-time confirmation of needle and catheter placement [13,14].

Although the benefits of ultrasound guidance in vascular access are well supported by evidence, its implementation in routine ED practice remains limited. Most studies have focused on critical care or surgical patients, or on central line placement, rather than peripheral access in general ED populations [13,15,16,17]. Moreover, the absence of standardized protocols and variability in staff training continues to be barriers to broader adoption [18,19].

In Spain, vascular access is considered a core nursing competency taught during undergraduate education, as stipulated in Law 16/2003 on the cohesion and quality of the National Health System. However, there is no unified national standard for nurse training in ultrasound-guided vascular access. Some institutions have developed internal training programs that have demonstrated favorable outcomes, showing that nurses can effectively perform ultrasound-guided PIVC insertion following specific education [20,21,22]. 

Several authors have argued that this training should begin during undergraduate education to better prepare future professionals [23].

This randomized clinical trial protocol aims to contribute new evidence regarding the effectiveness of validated tools for identifying DIVA and to assess the clinical benefits of ultrasound-guided vascular access in emergency care. In addition to evaluating procedural success, the study will assess pain associated with the technique and satisfaction levels reported by patients, families, and healthcare providers.

### Hypothesis and Objetive

The ultrasound-guided puncture facilitates vascular access in patients with difficult vascular conditions, identified using validated scales, who attend emergency departments.

The main objective of this study is to create a protocol for an RCT to compare ultrasound-guided techniques with traditional methods of vascular access in patients with DIVA identified by validated ED scales.

## 2. Materials and Methods

The study is designed as an open-label, randomized controlled trial (RCT) to be conducted in the emergency department (ED) of a secondary-level hospital in Spain. Recruitment is expected to begin in January 2025, with data collection concluding in December 2025. The trial protocol has been developed in accordance with the Standard Protocol Items: Recommendations for Interventional Trials (SPIRIT) [24] guidelines, ensuring a comprehensive and transparent study design. Upon completion, the results will be reported following the Consolidated Standards of Reporting Trials (CONSORT) [25] guidelines to ensure clarity and reproducibility. This protocol will be registered with ClinicalTrials.gov prior to participant enrollment.

### 2.1. Scope of the Study

The study will be carried out in the ED of the Hospital Nuestra Señora de Sonsoles (HNSS) de Ávila, belonging to the Regional Health Management of Castilla y León, Spain. This center has a catchment area of 158,140 inhabitants [26], which are spread over a total of 469 localities [27].

This population has an average age of 47.99 years with a dependency ratio of 42.56% for those under 65 and 63.20% for the total population. The population over 65 years of age constitutes 26.08% of the total population [26].

The HNSS ED receives about 47,000 emergencies per year (about 5000 pediatric patients), a figure that is increasing year after year. Some 34 nurses work in the ED in morning/evening/night shifts. The number of nurses per day is 6/7/5, respectively [28]. The nurses in the service have the official nationally recognized qualification, and therefore the necessary competences to perform vascular punctures. Prior to the study proposal, 99% were trained in the use of ultrasound-guided puncture by in-house training provided by nurses from the department who had acquired their skills and experience externally through regulated training.

### 2.2. Design

The RCT will collect data derived from the procedures performed on patients selected through probabilistic random sampling. The study workflow is outlined in the following flowchart (Figure 1). Following the CONSORT criteria, after an initial identification of the possible participants in the study, the inclusion and exclusion criteria will be applied, in order to subsequently assign each subject to the relevant group depending on the technique to be performed (PIVC or arterial punctures). Once the technique has been selected, using a randomized system, the subjects will be assigned to the Control or Experimental Groups, and the technique will be performed using the relevant procedure, using the traditional technique for CG and an ultrasound-guided technique for SG. After obtaining the required number of samples, the data obtained shall be analyzed.

### 2.3. Participants

The study will recruit DIVA patients identified using the A-DICAVE scale for patients aged > 14 years and the DIVA scale for those aged < 14 years, who attend the ED and require short PIVC or AGB.

Inclusion criteria:Prescription for CIP or GA cannulation.Informed consent signed by the patient or patient’s representative.A score ≥ 3 on the A-DICAVE scale or ≥4 on the DIVA scale for PIVC.

Exclusion criteria:Scores below 3 on the A-DICAVE scale or below 4 on the DIVA scale for PIVC.Inability to obtain informed consent from the patient or patient’s representative.

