### 3.1. Measurement Instruments

To identify DIVA patients during PIVC catheterization, two scales will be used depending on the patient’s age:

For patients aged ≥14 years, the A-DICAVE scale [11] will be applied. This scale consists of three items: vein visualization (scored 0–2), vein palpation (scored 0–2), and a history of puncture difficulty (scored 0–1). The total score is categorized as follows: easy (0–2 points) and difficult (3–5 points).

For patients aged <14 years, the DIVA4 scale [2] will be used. This scale, scored 0–10, includes four items: visible vein after tourniquet application (0–2 points), palpable vein after tourniquet application (0–2 points), age (≥3 years: 0 points; 1–2 years: 1 point; <1 year: 3 points), and history of prematurity with gestational age < 38 weeks (0–3 points). It has been demonstrated that scores > 4 typically indicate the need for multiple punctures to achieve adequate venous access.

In order to assess the level of satisfaction of professionals, patients and their families, an ad hoc instrument will be used, based on a 5-point Likert scale, ranging from 1 = “not at all satisfied” to 5 = “very satisfied”. Each item will be rated with a value from 1 to 5. To determine the general level of satisfaction, the following ranges of interpretation have been established:Not at all satisfied.Not very satisfied.Satisfied.Quite satisfied.Very satisfied.

To assess the satisfaction levels of professionals, patients, and their families, a 5-point Likert satisfaction scale will be applied. If patients are unable to express their satisfaction, only the response from their family members will be recorded.

Pain assessment will utilize numerical scales (0–10):○For adults and children aged > 7 years, the Visual Analogue Scale (VAS) [30] will be used.○For children aged < 5 years, the FLACC scale (Face, Legs, Activity, Cry, Consolability) [31] will be applied.○For adults with cognitive impairments, the PAINAD scale (Pain Assessment in Advanced Dementia) [32] will be employed.

Once the corresponding technique has been carried out, the data from the measuring instruments will be recorded through the form that will have the necessary items for their evaluation, together with the rest of the variables, as shown in Table 2.

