Evidence supporting the benefits of ultrasound-guided PIVC insertion is robust, with a meta-analysis by Tran et al. [37] demonstrating a significant improvement in first-attempt success rates. However, these studies were not conducted in ED settings, highlighting the need for research tailored to the unique demands of EDs. Our protocol aims to fill this gap by focusing on ED populations, where challenges such as high patient turnover and time constraints are prevalent.

Regarding pain assessment, while tools like the Visual Analog Scale (VAS) have been used to measure discomfort, they typically exclude pediatric patients or those with cognitive impairments. To ensure a comprehensive evaluation, our study includes alternative pain assessment scales suitable for a broader patient population, including those with cognitive challenges.

The use of ultrasound for arterial punctures in EDs remains underexplored, with most research focused on critical care or anesthesia settings [38,39]. However, studies such as that by Grandpiere et al. [3] have demonstrated that ultrasound guidance reduces the number of attempts and associated pain in difficult arterial access cases. Our study builds on this evidence, extending its focus to include patients with cognitive impairments and healthcare professional satisfaction.

The benefits of ultrasound-guided techniques extend beyond clinical outcomes, leading to a reduction in resource usage. Fewer attempts reduce material consumption and optimize staff allocation, contributing to faster procedures, shorter ED stays, and quicker test results [6,11,40,41,42]. Additionally, the increased efficiency enhances healthcare professional satisfaction and improves overall workflow in EDs.

While this study may face limitations, such as the inability to implement a double-blind design, random sampling and data coding ensure the reliability of our findings. The single-center design could also limit generalizability; however, the protocol’s methodological rigor allows for adaptation to other centers, providing flexibility for future studies.

In summary, this study addresses critical gaps in the literature by incorporating validated DIVA identification scales and ultrasound-guided techniques for PIVC and arterial access in ED settings. By considering confounding variables and focusing on a representative patient sample, our research aims to provide valuable evidence to enhance ED practices and improve patient care.

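### The arterial blood gas (ABG) population is defined inconsistently, and its sample size borrows an effect from difficult arterial access that no listed criterion selects

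*Protocol article*

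**What the plan says.** All places are in the protocol article.

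- **Section 2.3, lead sentence.** "The study will recruit DIVA patients identified using the A-DICAVE scale for patients aged > 14 years" (with the DIVA scale for younger patients), "who attend the ED and require short PIVC or AGB". Read alone, this requires a difficulty score for both procedures.
- **Section 2.3, criteria.** Inclusion: "A score ≥ 3 on the A-DICAVE scale or ≥4 on the DIVA scale for PIVC". Exclusion: "Scores below 3 on the A-DICAVE scale or below 4 on the DIVA scale for PIVC". Both are limited to venous cannulation (PIVC). The other listed conditions are a prescription for either procedure and consent.
- **Section 3.1.** "To identify DIVA patients during PIVC catheterization, two scales will be used depending on the patient’s age". The items are vein visibility, vein palpability, history of difficult puncture, age and prematurity. None rates an artery.
- **Hypothesis and main objective.** Ultrasound guidance "facilitates vascular access in patients with difficult vascular conditions, identified using validated scales". The main objective is likewise limited to DIVA patients identified by scale, and so is the conclusion in section 5.
- **Abstract.** It adds a separate objective on arterial puncture in the ED, with no difficulty restriction. It lists 114 DIVA subjects "along with 80 subjects from the general surgical area (GSA").
- **Section 2.4.** The ABG cohort is 80 (40 per group). It is planned from a cited study with a 34% difference in success, for a minimum difference of 37% in first-attempt success, 90% power, an alpha printed as 0.5% and 20% loss.
- **Section 4, Discussion.** The same cited study is described as showing that "ultrasound guidance reduces the number of attempts and associated pain in difficult arterial access cases".

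**The concern.** Eligibility decides whom a result is about, and here two readings of section 2.3 enrol different ABG patients. Staff who follow the lead sentence would require a vein score. Staff who follow the criteria would need only a prescription and consent. Neither reading selects difficult arterial access, because no arterial difficulty tool is named.

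Two things are at stake. First, an ABG result in patients not selected for difficulty could be reported under a hypothesis and a conclusion that speak only of scale-identified difficult access. Second, an effect seen where palpation often fails may be larger than the effect where it usually succeeds, so the size and power in section 2.4 may not carry over to the patients enrolled. This affects 80 of the 194 planned participants (114 + 80).

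**Working it through.** **1. The passages side by side**

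| Place | Population implied for ABG |
|---|---|
| 2.3 lead sentence | Scale-identified DIVA |
| 2.3 inclusion and exclusion criteria | Prescription and consent; no score |
| 3.1 use of the scales | Scales serve PIVC; items rate veins |
| Hypothesis, main objective, section 5 | Scale-identified difficult access |
| Abstract, ABG objective | Arterial puncture in the ED, no restriction |
| 2.4 with section 4 | Planning effect from difficult arterial access |

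The lead sentence conflicts with the criteria beneath it. The planning population in the last row is selected by no listed criterion.

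**2. The plan's own figure**

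Section 2.4 gives no arm rates, so 80 cannot be uniquely reproduced. I used the pooled-variance formula for two proportions:

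n per arm = [z(1−α/2)·√(2p̄(1−p̄)) + z(1−β)·√(p1(1−p1) + p2(1−p2))]² / (p2−p1)²

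Example with an assumed control rate of 0.49, so p2 = 0.86 and p̄ = 0.675, two-sided alpha 0.05 and power 90%:

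- 1.960 × √0.43875 = 1.298
- 1.282 × √0.3703 = 0.780
- (1.298 + 0.780)² / 0.1369 = 31.5, so 32 per arm
- 32/0.8 = 40 per arm, 80 in total

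At alpha 0.05 two-sided without continuity correction, the formula gives 31-33 per arm (76-84 in total, depending on how the loss is applied) for control rates of about 0.12-0.16 or 0.47-0.51. At the printed 0.5% two-sided, no control rate gives 80; a control rate of 0.50 needs 126 and 0.30 needs 148. The stated 80 therefore fits alpha 0.05 and an unstated control rate. The alpha mismatch with section 2.6 is a separate matter.

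**3. The ceiling**

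A 37-point gain needs palpation success of at most 100 − 37 = 63%. The document gives no palpation rate, so whether this binds is unknown.

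**4. Illustration for patients not selected for difficulty**

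Inputs:
- 40 × 0.8 = 32 evaluable per arm (section 2.4)
- two-sided alpha 0.05 (section 2.6)
- palpation success of 65-80% and a gain of 15-20 points (my assumptions; 80% can take only the 15-point gain, since 80 + 20 = 100)

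Power is the sum of the product of the two binomial probabilities over all outcome pairs in which the test rejects.

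| Palpation vs ultrasound | Chi-square | Fisher's exact |
|---|---|---|
| 65 vs 80% | 0.274 | 0.196 |
| 70 vs 85% | 0.305 | 0.215 |
| 75 vs 90% | 0.357 | 0.240 |
| 80 vs 95% | 0.480 | 0.276 |
| 65 vs 85% | 0.469 | 0.365 |
| 70 vs 90% | 0.532 | 0.411 |
| 75 vs 95% | 0.663 | 0.484 |

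The Fisher column matters because section 2.6 switches to that test when values below 5 occur. Expected failures in the ultrasound arm are 32 × 0.05 = 1.6, 32 × 0.10 = 3.2 and 32 × 0.15 = 4.8. They are below 5 in every row except 65 vs 80%, where they are 32 × 0.20 = 6.4.

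**The case against.** The strongest defence is that the design is coherent once read as two cohorts. The abstract lists 114 DIVA subjects and then a further 80, and gives ABG its own unrestricted objective. Section 2.2 separates patients by procedure before randomisation, section 2.4 sizes the cohorts separately, section 3.1 uses the scales for PIVC, and section 3.2 uses a separate form for each procedure. On this reading only the hypothesis, the main objective and the lead sentence of 2.3 are worded too broadly. Much of this stands, and it rules out several stronger inferences:

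- **That ABG patients need no difficulty score.** The criteria say so by omission, but the lead sentence of the same section says the opposite. The document contradicts itself and does not settle the matter.
- **That the ABG comparison answers no question the trial asks.** It validly answers the abstract's ABG objective. What it cannot support, if the criteria are applied as listed, is the DIVA hypothesis, main objective and conclusion.
- **That the 80 are surgical patients.** Only the number 80 links that label to the ABG cohort, and sections 2, 2.1 and 2.3 place the trial in the ED. It is probably a wording slip.
- **That the 37-point difference is unattainable, or that power is known to be low.** No arm rates are given, so neither can be shown.

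It is also fair to say that the account of the planning study rests on one Discussion sentence and cannot be checked here. It is, however, the protocol's own description of the source that it plans from. The defence does not explain why a cohort not selected for difficulty should be sized on that source. Nor is this a detail lost when an article condenses a full protocol: the criteria are printed, and they conflict with the sentence above them.

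**Conclusion.** The point holds as an inconsistency in the definition of the ABG population, together with a planning effect that does not match the listed criteria. Applied as listed, the ABG comparison is valid for ED patients who need an arterial gas. It cannot support claims about DIVA patients identified by scale, and the 37-point difference and 90% power are not justified for it. Applying the lead sentence instead would not repair this, because the scales chiefly rate veins and the document does not link them to arterial difficulty.

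The size of the loss of power is illustrative: about 27-66% by chi-square and 20-48% by Fisher's exact test. It rests on the assumed palpation rates and gains, 32 evaluable per arm and alpha 0.05. The stated 90% is attached to a printed alpha of 0.5%, so the two are not on exactly the same basis. The inconsistency itself rests on none of these assumptions. It should be corrected.

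**What to change.** Reconcile the abstract, the hypothesis and main objective, and sections 2.3, 2.4 and 3.1.

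- **Cheapest route.** State ABG as a separate objective in ED patients requiring arterial blood gas, not selected for difficulty. Limit the lead sentence of 2.3 to PIVC, and keep ABG out of the DIVA hypothesis and conclusion. In 2.4, give the arm rates, the planning difference and the power for that population.
- **If difficult arterial access is intended.** The sponsor must define it as an ABG eligibility criterion recorded before randomisation, and say why the cited effect applies to patients so selected.
- **Either way.** Correct the general surgical area label in the abstract as a wording error.

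The first route costs only wording and a restated calculation. Its downside is a narrower claim and probably a lower stated power. The second route changes who can be enrolled.
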